## Abstract

**Background:**

Motivational interviewing (MI) is an evidence-based, patient-centered communication method shown to be effective in helping persons with serious mental illness (SMI) to improve health behaviors. In clinical trials where study staff conducted lifestyle interventions incorporating an MI approach, cardiovascular disease (CVD) risk profiles of participants with SMI showed improvement. Given the disproportionate burden of CVD in this population, practitioners who provide somatic and mental health care to persons with SMI are ideally positioned to deliver patient-centered CVD risk reduction interventions. However, the time for MI training (traditionally 16-24 hours), follow-up feedback, and the coaching required to develop and maintain patient-centered skills are significant barriers to incorporating MI when scaling up these evidence-based practices.

**Objective:**

We describe the design and development of the following 2 scalable MI training approaches for community mental health practitioners: real-time brief workshops and follow-up asynchronous avatar training. These approaches are being used in 3 different pilot implementation research projects that address weight loss, smoking cessation, and CVD risk reduction in people with SMI who are a part of ALACRITY Center, a research-to-practice translation center funded by the National Institute of Mental Health.

**Methods:**

Clinicians and staff in community mental health clinics across Maryland were trained to deliver 3 distinct evidence-based physical health lifestyle interventions using an MI approach to persons with SMI. The real-time brief MI workshop training for ACHIEVE-D weight loss coaches was 4 hours; IMPACT smoking cessation counselors received 2-hour workshops and prescribers received 1-hour workshops; and RHYTHM CVD risk reduction program staff received 4 hours of MI. All workshop trainings occurred over videoconference. The asynchronous avatar training includes 1 common didactic instructional module for the 3 projects and 1 conversation simulation unique to each study’s target behavior. Avatar training is accessible on a commercial website. We plan to assess practitioners’ attitudes and beliefs about MI and evaluate the impact of the 2 MI training approaches on their MI skills 3, 6, and 12 months after training using the MI Treatment Integrity 4.2.1 coding tool and the data generated by the avatar-automated scoring system.

**Results:**

The ALACRITY Center was funded in August 2018. We have implemented the MI training for 126 practitioners who are currently delivering the 3 implementation projects. We expect the studies to be complete in May 2023.

**Conclusions:**

This study will contribute to knowledge about the effect of brief real-time training augmented with avatar skills practice on clinician MI skills. If MI Treatment Integrity scoring shows it to be effective, brief videoconference trainings supplemented with avatar skills practice could be used to train busy community mental health practitioners to use an MI approach when implementing physical health interventions.

**International Registered Report Identifier (IRRID):**

DERR1-10.2196/44830

## Introduction

### Background

Addressing inequities in cardiovascular health is a critical public health objective, particularly for persons with serious mental illness (SMI) who experience alarmingly high rates of cardiovascular disease (CVD) risk factors (obesity, hypertension, dyslipidemia, and diabetes mellitus) and risk behaviors (tobacco smoking, physical inactivity, and unhealthy diet) [1-4]. Lifestyle interventions, especially those that adopt a patient-centered approach, have been shown to be effective in helping persons with SMI to improve a wide range of health behaviors, including weight loss management, smoking cessation, and diabetes management [5,6]. A foundational approach for many of these lifestyle interventions is motivational interviewing (MI), which is an evidence-based, patient-centered communication method aimed at evoking patients’ motivations for change [7]. MI practitioners adopt a collaborative and empathic attitude, empower patients to act as an equal partner in their disease management, and use specific and core patient-centered communication skills to guide them toward change.

Patients’ CVD risk profiles improved significantly in clinical trials in which the study staff incorporated an MI approach to conduct lifestyle interventions among participants with SMI [8-12]. To lessen the disparity of CVD risk experienced by this population on a wider scale, evidence-based programs to improve cardiovascular health need to be implemented in community mental health settings where patients routinely receive their care [13]. Real-world practitioners in these settings need the training not only to deliver the CVD health intervention itself (the requirements of which will likely differ based on education and prior experience) but also for the specific preparation necessary to incorporate an MI approach. Although some mental health practitioners may have had previous exposure to MI, the method involves a complex skill set such that attending a seminar or a traditional 2- to 3-day in-person workshop alone is usually insufficient to build competency [14-16]. A meta-analysis of MI training studies suggested that for learners to gain and sustain MI skills after a workshop training, an average of 3 to 4 coaching sessions with performance feedback from practice sessions over several months were needed [17]. Yet, when scaling up evidence-based practices (EBP) for implementation research, the stated amount of training to deliver patient-centered behavior change lifestyle interventions may be harder to accomplish among practitioners in community mental health settings who have demanding caseloads and limited time for additional training activities [18]. Furthermore, because of the diverse occupational backgrounds of the health care team in these real-world community settings (which often include physicians, nurses, therapists, and frontline day program staff) [19], it is essential to develop MI training that is both tailored and acceptable to a variety of practitioners.

There are a few promising formats to efficiently train busy mental health care practitioners in MI [20]. Synchronous or real-time trainings over videoconferencing can be used to provide learners with a basic introduction to MI. Live videoconferencing, although still requiring coordinating schedules of learners and trainers, can simulate an in-person event. Videoconference trainings may be shorter than standard multiday trainings and can be broken into smaller chunks of time; this may be more appealing to managers and allows learners time to meet their other work demands. This format also allows practitioners the opportunity to reflect on and integrate the concepts they are learning between training sessions.

Web-based self-study programs that include video and workbook activities can be entirely asynchronous or may integrate a *live component* in which learners meet with trainers during scheduled times [21-23]. Both real-time synchronous and web-based training options have the advantage of being able to reach a wider audience of practitioners, including those working in rural settings or where skilled trainers of MI are not available, than in-person events. Both approaches reduce the travel time and cost for trainers and limit the need for learners’ transportation, workshop space, and other expenses associated with in-person workshops. When implementing the intervention at multiple locations, videoconference training provides a practical way to reach several sites simultaneously. Constraints around social distancing imposed during the COVID-19 pandemic have created the need for effective options other than traditional in-person trainings for teaching different counseling approaches. Although these modalities have been used more frequently in the past few years, research on the impact of web-based [22] and video trainings in MI remains limited [24].

Another scalable remote training format for MI involves the use of computer simulations [20,25,26]. SIMmersion [27] offers video-interface trainings; videotaped role-play conversations with human actors give learners the ability to practice and receive coaching and feedback on their recorded responses [20,28]. Avatar-interface programs, by contrast, provide learners with a virtual reality training experience to learn and practice their skills with simulated avatar patients [29,30]. Avatar trainings may involve a human trainer [31] or consist of fully automated, preprogrammed simulations; some platforms also offer coaching and feedback features to learners. Kognito [32] offers several avatar simulations in which the users enter an interactive virtual environment and engage in role-play conversations with emotionally responsive virtual humans on a variety of topics in health care, mental health, and patient-provider communication. Their approach combines the science of learning, the art of conversation, and the power of gaming technology. Avatar-interface programs can be used as stand-alone or as follow-up MI practice opportunities; they have the advantage of allowing learners to practice their skills in a convenient and private environment.

### Objective

Despite the many different approaches to training and the demonstrated effectiveness of MI [6], the amount and type of training necessary for real-world practitioners to develop and sustain proficiency in the method is uncertain [24]. In the context of 3 pilot implementation research projects that address weight loss, smoking cessation, and CVD risk reduction among persons with SMI, we aimed to develop scalable training in MI. This paper will provide a brief description of the 3 pilot projects; their corresponding setting and intervention; the design and development of the 2 MI training approaches, real-time brief workshops and follow-up asynchronous avatar training used to implement the EBP; and how we propose to evaluate the impact of the training on practitioners’ skills, attitudes, and beliefs about MI.

## Methods

### Implementation Pilot Studies Overview

The Johns Hopkins ALACRITY Center for Health and Longevity in Mental Illness is a research-to-practice translation center funded by the National Institute of Mental Health that aims to reduce premature mortality from CVD in people with SMI [33,34]. There is an untapped opportunity to develop scalable and generalizable solutions that integrate physical health care into mental health service sectors, which have not historically provided such services. Through the ALACRITY Center, we are conducting 3 pilot implementation projects in community mental health settings to study strategies for the adoption and integration of evidence-based CVD risk reduction interventions related to (1) weight loss; (2) tobacco smoking cessation treatment; and (3) hypertension, dyslipidemia, and diabetes care for people with SMI. This study is a substudy within the ALACRITY Center methods core and focuses on the 2 types of innovative MI training: real-time brief workshop training over videoconferencing and asynchronous avatar training, which span the 3 projects described in the following paragraphs.

ACHIEVE-D (Adapting an Evidenced-based Weight Management Intervention and Testing Strategies to Increase Implementation in Community Mental Health Programs) is a 6-month, 2-arm, weight loss pilot cluster randomized controlled trial (RCT), which is designed to assess the degree to which the implementation strategy, that is, performance coaching, impacts psychiatric rehabilitation program (PRP) coaches’ knowledge, self-efficacy, and fidelity to the delivery of the adapted ACHIEVE-D weight loss program curriculum when compared with a standard control group. ACHIEVE-D is a behavioral weight loss program designed for persons with SMI that provides basic weight loss health education using an MI approach, which was adapted from an intervention tested in a previous RCT [10,12,35]. Coaches in PRPs will be provided with the materials, trained on all aspects of the ACHIEVE-D weight loss curriculum, and encouraged to use MI skills in their interactions with the participants.

IMPACT (Promoting Evidenced-Based Tobacco Smoking Cessation Treatment in Community Mental Health Clinics) is a pretest-posttest design–based 12-month observational study that aims to examine the effects of an implementation intervention on mental health providers’ delivery of four EBP related to smoking cessation treatment for clients with SMI: (1) assessment of smoking status, (2) assessment of willingness to quit, (3) behavioral counseling, and (4) pharmacotherapy prescribing. Psychiatrists and mental health counselors at 5 community mental health clinics will receive training to implement smoking cessation practices, incorporating an MI style in their interactions with the patients. Counselors and prescribers will be encouraged to use MI to understand their patients’ smoking behavior and engage them in smoking cessation treatment.

RHYTHM (A Quality Improvement Process to Support Delivery of Cardiovascular Care in Community Mental Health Organizations) is a pretest-posttest design–based 12-month pilot study examining the effects of an adapted 5-step Comprehensive Unit–Based Safety Program implemented during care coordination aimed at reducing CVD risk for patients participating in behavioral health home programs [36]. Behavioral health home staff will receive the training necessary to implement the program, which will include the use of MI as a way of interacting with patients as they discuss various aspects of their patients’ CVD care.

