#### Analytic Plan

We will examine changes in the MITI from baseline to each subsequent time point to assess the change in practitioners’ skills in implementing MI. All SP interviews will be coded. A difference of 1 on a 5-point scale between pre- and posttraining scores for MITI global scores will be considered a clinically significant change in MI skills proficiency and will be used for statistical testing as the relevant effect size [42].

We will use a random 20-minute segment from the audiotaped SP interviews for coding as recommended by the creators of the MITI tool [42]. We will use a random calculator to ensure that the sampling of interviews that are >20 minutes is truly random so that proper inferences about the use of MI can be drawn.

We will examine changes in practitioners’ automated scores from completed avatar simulations from baseline to each follow-up time point.

We will also compare the associations of the MITI scores from the SP interviews with the Kognito-automated performance feedback metrics from a conversation simulation completed during the same time as the data collection window.

We will examine changes in participants’ beliefs about and the importance of using MI and their confidence to use its components with their patients.

Qualitative data from interviews and focus groups will be audio recorded and transcribed. Using thematic analysis [50], 2 research team members will identify meaningful segments within the responses and assign codes. We will then group these codes into themes, which will be examined by the research team.

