### Limitations

One limitation of the study is that none of the training methods have a comparator condition. The pretest-posttest outcomes are used here to assess the acceptability, feasibility, and effectiveness of the 2 training methods for improving practitioners’ MI skills.

Avatar practice requires practitioners to set aside time during their busy workdays. The extra workload and responsibilities of staff during the COVID-19 pandemic may leave little time or motivation for avatar skills practice after their initial exposure to MI, thus potentially decreasing the impact of this component of the training.

Another limitation is that because of the nature of the avatar platform and how the 3 conversations simulations are built, there are limited choice options. Therefore, after a learner has used the platform a few times, they might find it redundant and be less willing to practice. The didactic module and the conversation simulations may be a great opportunity for novice learners to practice their skills; practitioners with more experience in patient-centered counseling may be less interested in using a platform that offers few multiple-choice conversation options.

To overcome the challenges of assessing MI skills in implementation settings, we are using multiple measures, namely, MITI and the automated feedback scores from the avatar simulations. The feedback feature of the avatar simulations was originally designed to assist learners in improving MI skills. The mapping approach we used to create the automated scoring system for each of the global scores may limit the precision of the measure to capture how well the clinician is using MI. In addition, because participants complete the same simulations for training and assessment purposes, scoring from the simulations may not be a valid outcome measure of their MI skills.

This study design was in the context of implementation research and does not allow us to examine the effect of the MI workshop training component alone. However, examining MI in real-world settings is an innovative aspect of the study. Although there are limitations to asking about experiences of the training over a 6- or 12-month period, our qualitative interviews at the end of the study will add detail to the quantitative results.

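### ACHIEVE-D coaches are cluster randomised to performance coaching or control, yet MITI change is described without regard to arm and read as evidence on the two MI training methods, so any coaching effect would be attributed to workshop plus avatar

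*Protocol article*

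**What the plan says.** Under Implementation Pilot Studies Overview, the protocol article says that ACHIEVE-D "is a 6-month, 2-arm, weight loss pilot cluster randomized controlled trial (RCT"), and that it is "designed to assess the degree to which the implementation strategy, that is, performance coaching, impacts psychiatric rehabilitation program (PRP") coaches on "knowledge, self-efficacy, and fidelity to the delivery of the adapted ACHIEVE-D weight loss program curriculum when compared with a standard control group". The same section says that the weight loss programme "provides basic weight loss health education using an MI approach". Table 1 gives a single 4-hour MI workshop for all ACHIEVE-D staff, so MI training is common to both arms and performance coaching is what differs.

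The Analytic Plan then states: "We will examine changes in the MITI from baseline to each subsequent time point to assess the change in practitioners’ skills in implementing MI". No arm is mentioned. A 1-point change on a MITI global score is set as the clinically significant change and the relevant effect size. Data Collection places the ACHIEVE-D follow-up at 3 and 6 months.

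The Limitations state that "none of the training methods have a comparator condition" and that the pre-post outcomes serve to assess the acceptability, feasibility and effectiveness of the two training methods. They add that the workshop cannot be examined alone. The randomised performance coaching does not appear among the limitations.

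On coaching, the Background reports from a meta-analysis that, to gain and sustain MI skill after a workshop, "an average of 3 to 4 coaching sessions with performance feedback from practice sessions over several months were needed". The Strengths section repeats the argument and presents the avatar's automated feedback as filling the role of coaching.

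**The concern.** The question for ACHIEVE-D is what a brief videoconference workshop plus avatar practice does for MI skill. Some ACHIEVE-D coaches receive a further input, assigned by randomisation: performance coaching. If that coaching moves MITI scores at all, the combined-arm change from baseline mixes two things:

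- the change that accompanies workshop plus avatar;
- the coached share of coaches multiplied by the coaching effect.

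The article reads the total as evidence on the training methods. This bears on scalability, because the avatar is offered as a substitute for the human coaching that busy programmes cannot supply. An ACHIEVE-D result that silently includes performance coaching does not answer whether the substitute is enough.

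The same applies to the questionnaire on confidence to use MI. Self-efficacy is a named target of the performance coaching, and confidence is a close relative of it.

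**Working it through.** **Step 1. Reproduce the plan's own count.** Table 1 gives 21 (ACHIEVE-D), 35 and 51 (IMPACT prescribers; counselors and nurses) and 20 (RHYTHM).

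21 + 35 + 51 + 20 = 127, which matches the enrolment in Results. ACHIEVE-D's share is 21/127 = 16.5%. (The abstract gives 126 practitioners trained, which may be a different count; 21/126 = 16.7% changes nothing here.) The article gives no allocation ratio, number of clusters, SD or power figure to reproduce.

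**Step 2. Shift in the ACHIEVE-D mean if arm is disregarded.**

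Shift = coached share × coaching effect on a MITI global score.

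Neither input is in the article. I assume a coached share of 1/3 to 2/3 and an effect of 0.25 to 1.0 point. An effect of zero gives a shift of zero.

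| Coached share | Effect 0.25 | Effect 0.5 | Effect 1.0 |
|---|---|---|---|
| 1/3 | 0.08 | 0.17 | 0.33 |
| 1/2 | 0.13 | 0.25 | 0.50 |
| 2/3 | 0.17 | 0.33 | 0.67 |

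The range is 0.08 to 0.67 point against the 1-point threshold. For example, with half the coaches coached and an effect of 0.5, a change of 0.75 without coaching would appear as 0.75 + 0.25 = 1.0 and meet the threshold.

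**Step 3. Shift in a mean pooled over all 127.** Multiply by 21/127:

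- smallest: 1/3 × 0.25 × 21/127 = 0.01;
- half coached, effect 0.5: 0.25 × 21/127 = 0.04;
- half coached, effect 1.0: 0.50 × 21/127 = 0.08;
- largest: 2/3 × 1.0 × 21/127 = 0.11.

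The article does not say whether the projects are pooled. If they are, the shift is small.

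**Step 4. What an arm comparison could show.** Assume an even split of 21 (10.5 per arm, divided by the design effect), an SD of 0.8 to 1.2, a design effect of 1.0 to 1.5, and a two-sided 5% test by normal approximation. Power is 34% to 82% for a 1-point difference and 12% to 30% for 0.5 point. The comparison is descriptive, not confirmatory.

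**Step 5. Precision of a control-arm estimate.** Leaving clustering aside, the standard error grows by √(21 / control-arm n):

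- one third coached (14 controls): √(21/14) = 1.22;
- half coached: √(21/10.5) = 1.41;
- two thirds coached (7 controls): √(21/7) = 1.73.

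**The case against.** The strongest reply has four parts.

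1. **Silence is not a choice.** The Analytic Plan specifies no model for any outcome, so not mentioning arm neither commits to combining the arms nor rules out reporting by arm. Model terms are commonly left to a full protocol or analysis plan, and none is shown. This stands as far as the model goes. It does not cover the attribution: the article itself says what the pre-post change will be used to judge, and lists what the design cannot separate without naming the coaching.

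2. **The coaching may not touch MI.** Its stated targets are knowledge, self-efficacy and curriculum fidelity. The article's evidence on coaching concerns coaching in MI skills, and it counts only workshop and avatar as MI training. Nor does it say when performance coaching starts or how often it occurs. This stands. A reader might infer that coaching effects definitely will be credited to the training; the article supports only that any such effect would be. Spillover is plausible because the curriculum is delivered with an MI approach.

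3. **There is no conflict over the comparator.** A reader might take the Limitations to deny the randomised control group. They do not: the statement concerns the training methods, which both arms receive. Nor does the article support a complaint that a randomised contrast is wasted, since that contrast is ACHIEVE-D's own question and this substudy is about MI training.

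4. **The control arm is no clean estimate either.** It remains an uncontrolled pre-post change that includes repeat testing, time trends and curriculum training. With 21 coaches and an unstated number of programmes, a model with arm-by-time terms and a programme random effect may be poorly estimated. Both points stand and limit the remedy to simple reporting by arm.

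**Conclusion.** The point holds in conditional form and is of moderate weight. As the article is written, any effect of the randomised performance coaching on MITI would be read, within ACHIEVE-D, as an effect of workshop plus avatar, and the Limitations do not warn of this. Under the assumed shares and effects the ACHIEVE-D mean change shifts by 0.08 to 0.67 point. The upper part of that range could carry a change below threshold past the 1-point mark; at zero effect there is no distortion.

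A reader might infer that the study's overall conclusion is at risk. The figures do not support that: ACHIEVE-D is 21 of 127 practitioners, and a fully pooled mean moves by 0.01 to 0.11 point. The harm is confined to ACHIEVE-D's own results. Whether an unseen analysis plan already reports by arm cannot be judged from the article.

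**What to change.** - State whether performance coaching covers MI skills and when it runs relative to the 3- and 6-month interviews.
- Report ACHIEVE-D change in MITI, and in confidence to use MI, separately by randomised arm.
- Take the control-arm change as the ACHIEVE-D estimate for workshop plus avatar without performance coaching, and say that it remains an uncontrolled pre-post estimate.
- Give the difference between arms descriptively, acknowledging that programmes, not coaches, were randomised. A mixed model is not needed for this.
- Include arm in any analysis that pools the three projects.
- Name the coaching co-intervention in the Limitations.

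This takes a few sentences and no new data, since arm is already recorded by the randomisation. The cost is precision: the ACHIEVE-D estimate without coaching rests on only the control-arm share of 21 coaches, with a standard error about 1.2 to 1.7 times that of the combined group under the shares assumed above, before any allowance for clustering.
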